### 6.1. Protocol for Carrying out the DPM Intervention (Intervention Fidelity)

The DPM protocol would include: (1) the goal of the DPM; (2) special contents and activities of each DPM and specific instructions for each session. This protocol will be read and signed by the research assistant (for the experimental group) before each DPM session to ensure consistency.

To optimize fidelity, several strategies will be used. First, the research assistant will train the research team to lead the DPM. Second, a detailed teaching manual and questions for digital-based activities were developed and tested. Third, the research assistant will participate in biweekly meetings with the research team to discuss and review cases and receive “booster” sessions on pain management education. Fourth, a process evaluation, fidelity checklist, and semi-structured interview will be employed.

### 6.2. Protocol for the Control Group

The participants in the control group will receive the usual care and a pain management pamphlet. We believe that reading the pamphlet could help the participants to manage their pain but would be less efficacious than the DPM.

### 6.3. Protocol for the Preparation of NECs and the Collaboration Plan

The face-to-face sessions will be carried out in a multi-function room/larger room, preferably with comfortable chairs, adequate lightning, and good ventilation. NEC staff will ensure that the older adults and their caregivers are wearing comfortable clothing when participating. Additionally, the research team will alert the NEC staff and work with them to ensure environmental safety, reduce fall risks, and improve the mobility of all participants. In light of the COVID-19 situation, we would introduce modifications if necessary, including replacing the center-based activities with sessions held over Zoom/online-based contact. This would be possible because the informal carers would have a smart phone with access to the Internet. The research team, with the help of the NEC staff, can contact the informal carer via phone and link up to Zoom for center-based activities and further actions.

## 7. Data Collection and Outcome Measures

A 36-month timeline is essential to recruit the required sample. Data collection will be carried out simultaneously in multiple sites.

Data will be collected at three time points: At baseline (T0), week 8 (T1), and week 16 (T2), using standardized methods and questionnaires, with a follow-up assessment (T2) to determine whether the observed benefits can be sustained over a longer period of time.

### 7.1. Primary Outcome

Pain intensity:

The Chinese version of the Brief Pain Inventory will be used to assess the multidimensional nature of pain, including intensity and interference with life activities in the previous 24 h [22]. Coefficient alphas for the pain severity and pain interference items were 0.894 and 0.915, respectively [22].

### 7.2. Secondary Outcomes

2.Pain self-efficacy:

A Chinese version of the Pain Self-Efficacy Questionnaire (PSEQ) will be used to measure self-efficacy in coping with activities despite pain [23]. It consists of 10 statements about a person’s confidence in performing 10 activities or tasks despite experiencing pain. Higher scores indicate stronger self-efficacy beliefs. The test–retest reliability coefficient was 0.75, and the Cronbach’s alpha for internal consistency was 0.95, showing that the tool is reliable [23].

3.Perceived quality of life:

The Chinese version of the EQ-5D-5L [24] will be used to measure the quality of life of the participants as well as the cost effectiveness of the proposed dyadic pain management program. EQ-5D-5L is a health-related quality-of-life measure developed by the EuroQol Group. It is based on a descriptive system that defines health in terms of five dimensions: Mobility, Self-Care, Usual Activities, Pain/Discomfort, and Anxiety/Depression. Each dimension has three response categories corresponding to no problems, some problems, and extreme problems. EQ-5D-5L has been widely tested and used in the general population and patient samples and has been translated into over 130 different languages.

The EQ-5D-5L has been validated and used in the Hong Kong context in clinical and cost-effectiveness studies. A comparison of scores (e.g., a value set from 1 (full health) to 0 (dead)) reflects an estimation of quality-adjusted life years (QALYs) before and after the intervention; with reference to the Hong Kong norm, this would provide evidence of the effectiveness and cost-effectiveness of the proposed dyadic pain management program for community-dwelling older adults with chronic pain.

4.Psychological health: Depression, anxiety, and stress:

The Depression Anxiety Stress Scales 21-items (DASS-21) is a self-administered psychological instrument to evaluate degrees of depression, anxiety, and stress [25]. Every part has seven items on a 4-point Likert scale ranging from 0 to 3. The Cronbach’s α was 0.912 and the test–retest Pearson correlation coefficient was 0.751 [25].

5.Caregiver burden inventory (for the caregivers only):

The Caregiver Burden Inventory [26] comprises 24 items measuring five dimensions of burden related to the caregiving role. These are: (1) time-dependence; (2) developmental burden; (3) physical burden; (4) social burden; and (5) emotional burden. Participants are asked how often each statement describes their feelings on a scale ranging from 0 (never) to 4 (nearly always). Alpha coefficients for each subscale were satisfactory and ranged from 0.74 to 0.88. The overall internal consistency was a = 0.91.

6.Process evaluation:

A process evaluation will be carried out to identify the strengths and limitations of the intervention from the perspectives of the older adults and their caregivers. The results will help the research team to understand the therapeutic features of the DPM and the barriers and difficulties faced by the participants. This will increase our understanding of the processes underlying the effects of the intervention and explain how it works best in practice. The timing and methods of data collection will include:
Field observations:

These will be carried out in the NECs to monitor the quality of the implementation of the DPM. Each DPM will be observed twice (by random selection among the four sessions) when carrying out the DPM. A total of 48 observations will be conducted by the principal investigator, guided by a fidelity checklist. The fidelity checklist was developed based on a similar intervention study for chronic pain [9]. The checklist indicates the implementation of the DPM in terms of four levels: low/not observed; observed to a small degree; observed to a medium degree; and high implementation. To ensure quality and consistency, the research assistant should demonstrate 95% implementation at a high level [23]. The compliance rate will be calculated. Field notes will also be taken on outstanding events. The data will be examined to determine whether the research assistant carried out the implementation according to the teaching manual and protocol.

Knowledge and skills acquired in managing pain situations for older adults:

A questionnaire will be given to the participants in the experimental and control groups regarding their knowledge and skills in managing pain situations at baseline (T0), week 8 (T1), and week 16 (T2).

Semi-structured interviews for older adults and their caregivers:

Individual interviews will be conducted by the RA1 within 2 weeks after T1 (post-test). We will recruit 8 older adults and their caregivers (20%) from the experimental group and 8 (20%) from the control group, or until data saturation is reached. To obtain the widest range of opinions and comments from different perspectives, equal proportions of participants (1) with significant positive changes between the baseline and first post-test measurements, (2) without significant changes, and (3) with negative changes will be invited for interviews. They will be asked to comment on their experiences and feelings about the intervention that they received and on changes in their behavior; their perceptions of the intervention; their beliefs, concerns, and views of the difficulties of managing pain; and on how the intervention could be improved to meet their needs.

A semi-structured interview guide was developed for interviews in Cantonese. Participants will be asked about their experiences in joining the DPM; the perceived benefits, limitations, and barriers to pain management; its usefulness; and recommendations for improving the DPM.

A SPIRIT figure is used to illustrate the timepoints for enrolment, interventions, and assessment (Table 1) [27].

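### Section 7.2 gives the EQ-5D-5L three response levels, and treats a before-after score comparison referred to a norm as evidence of QALY gain and cost-effectiveness

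*Protocol article*

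**What the plan says.** Section 7.2 (Secondary Outcomes, perceived quality of life) makes two sets of statements.

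- **Instrument.** "The Chinese version of the EQ-5D-5L [24] will be used to measure the quality of life of the participants", and "It is based on a descriptive system that defines health in terms of five dimensions". It then says: "Each dimension has three response categories corresponding to no problems, some problems, and extreme problems". No value set is named. The scale is illustrated only as "a value set from 1 (full health) to 0 (dead").
- **Use.** The instrument is also to measure quality of life "as well as the cost effectiveness of the proposed dyadic pain management program". A comparison of scores "reflects an estimation of quality-adjusted life years (QALYs) before and after the intervention"; and, "with reference to the Hong Kong norm, this would provide evidence of the effectiveness and cost-effectiveness of the proposed dyadic pain management program".

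Four other places bear on the point.

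- The aim in section 2 sets the programme against a usual-care control population and includes quality of life. Cost-effectiveness is not among the listed objectives.
- Section 6.2 gives the control arm usual care and a pamphlet.
- Table 1 schedules quality of life at baseline (T0), week 8 (T1) and week 16 (T2).
- Section 8 puts quality of life in a multilevel regression over those three times, or in a Generalized Estimating Equation with within-group and between-group comparisons. It accounts for clustering by center.

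**The concern.** There are two faults, and they are separate.

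**Level count.** The name of the instrument signals five dimensions and five levels. The description has the five dimensions but only three levels. A three-level and a five-level form need different value sets, so a reader cannot tell from the text which form will be given or how it will be scored.

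**Inference.** Section 7.2 draws effectiveness and cost-effectiveness from a before-after comparison and a population norm. The sentence does not mention the randomised control arm. Under section 5, older adults and caregivers both enter with a pain score of at least 2, so their later scores can improve through regression to the mean and natural change without any effect of the programme. A utility score is also not a QALY until time is brought in, and no quantity of utility data supplies the cost side of a cost-effectiveness result.

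At stake is what the trial may conclude from its EQ-5D data: a QALY gain credited to the programme that the control arm may share, and a cost-effectiveness claim with nothing on the cost side.

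**Working it through.** The article states no QALY figure, so there is none to reproduce. The checks are on the description and on the logic of the contrast.

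**1. Levels.** Inputs from section 7.2: 5 dimensions, 3 levels as described, 5 levels as the name implies. Number of health states = levels^dimensions.

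- As described: 3^5 = 243.
- As named: 5^5 = 3125.

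The two descriptive systems differ, so a profile from one cannot be looked up directly in the other's value set. This shows that the text conflicts with itself. It does not show that any score will be wrong.

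**2. Before-after against between-arm QALYs.** Times come from section 7: weeks 0, 8 and 16. The utilities are assumptions, because the article gives none: baseline 0.70 in both arms, and an intervention-arm gain g of 0.05 to 0.10 reached at week 8 and held to week 16.

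QALYs are the area under the utility curve, by trapezoids, divided by 52. The gain over own baseline is

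(8 × g/2 + 8 × g) / 52 = 12g / 52.

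- g = 0.05: 0.60 / 52 = 0.0115.
- g = 0.10: 1.20 / 52 = 0.0231.

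If the control arm gains c on the same pattern, the between-arm difference is 12(g − c) / 52.

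| Control-arm gain c | Before-after QALY gain (intervention arm) | Between-arm QALY difference |
|---|---|---|
| 0 | 0.0115 to 0.0231 | 0.0115 to 0.0231 |
| g/2 | 0.0115 to 0.0231 | 0.0058 to 0.0115 |
| g | 0.0115 to 0.0231 | 0 |

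The middle column does not move, so the before-after figure cannot tell a full effect from no effect. For scale, full health throughout 16 weeks is worth 16/52 = 0.308 QALY.

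**3. Cost-effectiveness.** The ratio is incremental cost divided by incremental QALYs. It has no value without a cost. With an assumed incremental cost of 500 to 2000 currency units per person:

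- lowest: 500 / 0.0231 = about 21,700 per QALY (g = 0.10, c = 0);
- highest finite value in the table: 2000 / 0.0058 = about 346,700 per QALY (g = 0.05, c = 0.025; computed with the unrounded 0.00577);
- undefined where the between-arm difference is 0.

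These inputs are illustrative only. The same utility gain in the intervention arm is compatible with very different conclusions, depending on the control arm and on cost.

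**The case against.** Four stronger readings are tempting, and the article does not support them.

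- **That the EQ-5D utilities will be wrong for everyone.** The article commits to the Chinese EQ-5D-5L, cites a source for it and writes no three-level scoring rule. If the five-level form is given and scored with its own value set, the error is one descriptive sentence.
- **That the trial ignores its control arm for quality of life.** Section 8 includes quality of life in the clustered model over T0, T1 and T2, with between-group comparison, and the aim in section 2 is comparative. The randomised quality-of-life effect is planned. Reference to the Hong Kong norm may also mean local values rather than a substitute comparator.
- **That utilities are floored at 0.** The range from full health to dead is offered as an example and names two anchors. It sets no minimum.
- **That no costs will be collected.** Section 7 and Table 1 list no cost item, but a condensed article may leave costing to a fuller document. The absence is not a fault in itself.

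These objections limit the point but do not remove it. The level count is still misstated for a listed secondary outcome. The article also affirms, rather than merely omits, that score comparison supplies evidence of cost-effectiveness, and it describes QALYs through a weaker contrast than the one in its own analysis section. Section 7.2 and section 8 should agree.

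**Conclusion.** The point holds in two limited parts.

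- **Level count:** a definite contradiction within section 7.2 (243 against 3125 states). Its effect on the data is conditional: none if the five-level form and a matching value set are used, and affecting all EQ-5D utilities if a three-level form or three-level scoring is used. The text does not settle which.
- **Inference:** the statement that before-after scores, referred to a norm, give QALY evidence of effectiveness and cost-effectiveness is wrong as written. In the illustration, an apparent gain of 0.0115 to 0.0231 QALY goes with a between-arm difference anywhere from zero to the full amount. This rests on the assumed baseline of 0.70, gains of 0.05 to 0.10 and the assumed time pattern. The logical conclusion depends on none of them.

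The scope is one secondary outcome and the claims drawn from it. The primary outcome, the sample size and the planned between-arm quality-of-life comparison are unaffected.

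**What to change.** 1. In section 7.2, state five response levels, or correct the instrument name if a three-level form is meant. Say that scores will use the value set matching the version given, and name it.
2. Replace the before-after and norm statement with the between-arm difference in QALYs over 16 weeks, computed from the T0, T1 and T2 utilities, adjusted for T0 utility and analysed in the clustered model of section 8. If the norm is kept, present it as description only.
3. Delete the statement that score comparison gives evidence of cost-effectiveness, or limit it to an incremental analysis that uses costs from both arms.

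Cost: items 1 and 2 need wording and a little more analysis but no new data, because quality of life is already scheduled at all three times. Item 3 means a weaker claim, or cost data from both arms if these are not already planned elsewhere.

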## 8. Results Analysis

IBM-SPSS version 22 will be used to perform statistical analyses. One member of the research team is a statistician and will discuss the data analysis with the team. Descriptive statistics (frequency%; mean (standard deviation)) will be used to describe the demographic data of the participants.

An intention-to-treat analysis will be conducted for any missing data. A Kolmogorov–Smirnov normality test will be used to examine the normality of the variables. To examine the effects of the intervention, a multilevel regression will be used to compare pain intensity, pain self-efficacy, the use of drug and non-drug methods of pain relief, quality of life, and the knowledge and skills acquired in managing pain situations at baseline (T0), week 8 (T1), and week 16 (T2) if the data are normally distributed. A Generalized Estimating Equation will be used for within-group and between-group comparisons if the data do not follow a normal distribution. A Cohen’s d effect size of the intervention effect will be calculated for all outcomes. A *p*-value of <0.05 will be considered statistically significant. As for a cluster RCT analysis, it is suggested that both a multilevel regression and a generalized estimating equation be used, as they are capable of handling clustered data. Observations from the same participant will fall into a level, and participants from the same NEC will fall into a level, so that both within-subject correlations and intra-cluster correlations can be accounted for.

A qualitative analysis of the contents of the interview data and the WhatsApp text messages will be conducted. The tape-recorded interview data will be transcribed by RA1 and cross-checked for accuracy by the PI or one CI. Finalized transcripts will then be independently coded by two CIs, and important manifest contents and latent meanings in the data will be identified. To achieve consistency and agreement on the meaning of the data, the research team will compare, discuss and agree on codes, and then combine them with verbatim data to form categories/subcategories describing the older adults’ and caregivers’ experiences and perceptions of the benefits and difficulties of participating in the DPM.

For WhatsApp text messages, responses to reminders, questions, and discussions will be organized into themes. A set of categories/subcategories with supporting text message data will be generated to describe the strengths and limitations of the DPM and further improvements that could be made to the DPM.

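### A Kolmogorov–Smirnov test on raw scores chooses between a multilevel model and GEE, and a later sentence suggests both, so the primary analysis is not fixed in advance

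*Protocol article*

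**What the plan says.** All of this is in section 8 (Results Analysis) of the protocol article.

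- **The gate:** "A Kolmogorov–Smirnov normality test will be used to examine the normality of the variables".
- **If the test passes:** a multilevel regression compares the outcomes "at baseline (T0), week 8 (T1), and week 16 (T2) if the data are normally distributed". The list includes pain intensity, the primary outcome.
- **If it fails:** "A Generalized Estimating Equation will be used for within-group and between-group comparisons if the data do not follow a normal distribution".
- **A few sentences later, in the same paragraph:** "it is suggested that both a multilevel regression and a generalized estimating equation be used, as they are capable of handling clustered data".
- **Levels:** "Observations from the same participant will fall into a level, and participants from the same NEC will fall into a level". The stated aim is to account for both within-person and within-NEC correlation.
- **Missing data:** "An intention-to-treat analysis will be conducted for any missing data".
- **Test level:** a p-"value of <0.05 will be considered statistically significant".

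Section 3 makes the NEC the unit of randomization. Section 4 gives three counts of NECs (20, 22, and 12 per arm), about 7 dyads per NEC and 20% drop-out.

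**The concern.** There are four linked problems.

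1. **The primary model is not unique.** One rule says either model, depending on a test of the data; a later sentence suggests both. Nothing says which p-value answers the primary objective on pain, and the gate can send different outcomes down different branches.
2. **The gate tests the wrong quantity.** A linear mixed model assumes roughly normal residuals and random effects. The raw scores need not be normal, and a coarse or bounded scale can fail the test while the model is adequate.
3. **The fallback swaps one assumption for another that this design meets less well.** With an identity link, GEE targets the same mean difference. It drops the normality assumption, but its robust standard error is justified by a large number of clusters, and this trial has 20 to 24.
4. **The switch changes the missing-data assumption without saying so.** A likelihood-based mixed model is valid under missing at random (MAR). Unweighted GEE needs, in essence, missing completely at random. Intention-to-treat defines who is analysed and in which arm; it is not a method for missing values.

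At stake are the type I error of the primary test and the reader's ability to identify which result was the planned one.

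**Working it through.** The plan gives no operating characteristic for this rule, so there is no figure to reproduce. The benchmark is the nominal 5%, taken as two-sided (sidedness is not stated).

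**Inputs from section 4.** NECs: 20, 22 (150/7 = 21.4, rounded up) or 12 + 12 = 24. Cluster size about 7. Drop-out 20%. Difference 1.6, SD 2.1.

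**Step 1. Is one model fixed?** Set side by side, the two branch sentences make the methods alternatives, while "it is suggested that both a multilevel regression and a generalized estimating equation be used" makes them joint. Both cannot hold for the primary result, and no sentence ranks them.

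**Step 2. Type I error of the GEE branch.** Take k equal-sized NECs per arm, treatment at NEC level and GEE clustered on NEC. The estimate is the difference of arm means. The uncorrected sandwich variance divides the between-NEC sum of squares by k² where the usual t test divides by k(k − 1). The Wald statistic is therefore t × √(k/(k − 1)), with t on 2k − 2 df, and

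type I error = P(|t with 2k − 2 df| > 1.96 × √((k − 1)/k)).

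| NECs | k | Threshold | df | Type I error |
|---|---|---|---|---|
| 20 | 10 | 1.859 | 18 | 7.9% |
| 22 | 11 | 1.869 | 20 | 7.6% |
| 24 | 12 | 1.877 | 22 | 7.4% |

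The excess is 2.4 to 2.9 percentage points. Simulation with skewed data, unequal clusters, 7 dyads per NEC and 20% loss (5,000 runs per setting; intra-cluster correlation 0.001 as in the plan, 0.05 and 0.10 as assumptions) gave 7.1–8.8%. An NEC-level t test on the same skewed data gave 4.5–5.4%. In these settings the number of clusters did the damage, not the shape of the data. For equal clusters, a bias-corrected variance with a t reference on K − 2 df (K = total NECs) returns exactly 5%.

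**Step 3. What decides the branch?** Normal scores were simulated with SD 2.1 (section 4), n = 120–150 and assumed means.

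| Score | Plain K–S rejects | With Lilliefors correction |
|---|---|---|
| Whole points, mean 5 | 47–72% | 100% |
| Quarter-point mean, mean 5 | 0.1% | 12–15% |

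Moving the assumed mean toward the scale floor raises the Lilliefors figure for the quarter-point score, to at most about 38%. The underlying distribution is normal throughout, so the branch is being chosen by rounding, scale limits, sample size and test version. Section 7.1 does not say how the pain intensity score is formed.

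**Step 4. Missing data.** The setting was no true effect, 22 NECs, and 20% drop-out before week 16 depending on the observed week-8 score in opposite directions by arm. That pattern is an assumption and deliberately strong.

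| Estimator | Bias, points |
|---|---|
| GEE, independence working correlation | −0.54 to −0.58 |
| GEE, exchangeable within participant | −0.03 to −0.07 |
| Likelihood-based | at most about 0.05 in size |

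Against the planning difference of 1.6, the first row is 0.54/1.6 = 34% to 0.58/1.6 = 36%. The second row is of the same order as the likelihood estimates. A mixed model is not safe by default either: one with only a participant intercept and no NEC level rejected in 8.5–11.8% of about 300 runs.

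**The case against.** The strongest defence has five parts.

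- **GEE really does remove the normality assumption.** This stands. A reader might infer that GEE offers nothing against non-normality; that is wrong. The objection to GEE here is the number of clusters.
- **The NEC is named as a level.** This stands. A reader might infer that GEE would cluster on participants alone and have a larger error at higher intra-cluster correlations. Section 8 says both levels are to be accounted for, so such error rates do not apply.
- **The gate may seldom choose GEE.** This largely stands. A reader might infer that GEE would often be selected. The high rejection rates belong to whole-point scores, whereas section 7.1 names the Brief Pain Inventory and reports reliability for several severity items, so a multi-item score is plausible. The entry cut of at least 2 is on the Numeric Rating Scale at enrolment and does not truncate Brief Pain Inventory scores at weeks 8 and 16. If the gate were independent of the test result, 15% selection would give 0.85 × 5% + 0.15 × 7.9% = 5.4% overall. The figure approaches 7.9% only if the gate nearly always rejects.
- **Variance corrections, working correlation and missing-data methods are usually left to a full plan.** This is fair, so their absence is not the point. The gate and the sentence suggesting both are stated rules, and they are.
- **The sentence suggesting both may only mean that either method handles clustering.** This is a possible reading. It leaves an ambiguity that still has to be removed, and the gate remains under either reading.

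**Conclusion.** The concern holds in this form and should be fixed. Section 8 lets a normality test on raw variables choose the primary model and then suggests using both, so the primary result is not uniquely identified before data are seen. That conclusion rests on the text alone.

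The numerical harm is moderate and conditional. When GEE is selected and tested with an uncorrected robust Wald statistic, type I error is about 7.4–7.9% at a nominal 5% for 24 down to 20 NECs, assuming equal clusters and NEC-level clustering. How often GEE would be selected is unknown, because it depends on how pain is scored and which version of the test is run.

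A reader might infer that a switch to GEE would seriously bias the result under the expected 20% drop-out. The documents do not support that: the large bias needs an independence working correlation and strong drop-out that differs by arm, and neither is stated.

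**What to change.** In section 8:

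1. Delete the Kolmogorov–Smirnov gate and the sentence suggesting both methods.
2. Name one primary model for the continuous outcomes: a linear mixed model with NEC and participant levels and small-sample degrees of freedom (Satterthwaite, for example; other small-sample methods would also serve).
3. Replace the missing-data sentence with two statements: all randomised older adults are analysed in their allocated arm, and missing outcomes are handled by likelihood under MAR.
4. Check residuals as a diagnostic that does not change the primary model.
5. Keep GEE, if wanted, only as a sensitivity analysis clustered on NEC, with a small-sample corrected standard error and a t reference on K − 2 df.

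The NEC counts in section 4 (20, 22 and 24) should be reconciled at the same time, since K sets those degrees of freedom.

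The cost is wording in the analysis section, with no change to design, recruitment or data collection. The one drawback is slightly wider confidence intervals than uncorrected GEE would report.
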